###### Confidentiality

During or at the conclusion of the research, the data collected on the individuals who are the subject of the research and transmitted to the sponsor by the investigators (or any other specialized parties) will be rendered non-identifying.

Under no circumstances may the names of the persons concerned or their addresses appear in clear text..

Only the initials of the surname and first name will be recorded, accompanied by a coded number specific to the research indicating the order of inclusion of the subjects.

The sponsor will ensure that each person who takes part in the research has given his or her consent to access individual data concerning him or her and strictly necessary for the quality control of the research.

###### Retention of documents and data

Research documents and data will be retained for up to 2 years after publication.

11/14

###### STATISTICAL ASPECTS

- 1. **Statistical justification of the sample size**

This retrospective study does not require a specific size calculation.

###### Description of the statistical methods

The 2 groups will be defined according to the number of consultations honored each year over a 2-year period. Patients who have attended at least an average of 2 consultations per year for 2 years, i.e. a minimum of 4 sessions over 2 years, will be included in the experimental group Patients who do not reach this number will be included in the control group.

The categorical variables will be presented by their numbers and percentages, and compared by Fisher's exact tests or chi2. Quantitative variables will be presented by their median and interquartile range, or by their mean and standard deviation, and compared by t-tests or Wilcoxon tests, depending on their distribution

The rates of recurrence, hospitalization, pedicure follow-up and adapted footwear will be compared between the 2 groups by Fisher exact tests.

The time to recurrence in each group will be measured by the Kaplan-Meier estimator, and compared between the 2 groups by a log-rank test. If the conditions for application are met, the time to recurrence will be analyzed by a multivariate Cox regression model taking into account the characteristics of the patients (age, sex, length of diabetes, presence of arterial disease, neuropathy) as well as whether or not they were followed up in a "foot in remission" consultation, whether they had pedicures and whether they wore adapted shoes.

The results of the multivariate Cox regression study took into account the characteristics of the patients (age, sex, length of diabetes, presence of arterial disease, neuropathy) as well as whether or not they were followed up in a "foot in remission" consultation, whether or not they had received pedicure and whether or not they wore adapted shoes.

All tests will be performed in a two-sided manner, with a 1st species risk alpha fixed at 5%. The statistical analysis will be performed by [name] of the Clinical Research Unit of the CHSF, using the R software (R Core Team (2021). R: A language and environment for statistical computing. R Foundation for Statistical Computing, Vienna, Austria. [https://www.R-project.org/](http://www.R-project.org/))).

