#### OBJECTIVES

- 1. **Primary objectiv**

To evaluate the benefit of a specific multidisciplinary follow-up of the healed diabetic foot at the rate of 2 annual consultations on wound recurrence.

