#### Primary outcome

Foot wound recurrence at 2 years

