#### Secondary outcomes

- Hospitalization for foot wound at 2 years
- Pedicure follow-up at 2 years
- Wearing suitable footwear at 2 years
  1. Type of study

Monocentric retrospective cohort study, observational study.

9/î4

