###### Nature of data collected

- Verification of inclusion criteria

- Age and gender

- Type and duration of diabetes

- Presence of arterial disease, diabetic neuropathy

- History of amputation

- HbAlC

During the 2-year observation period from the date of recovery:

- Number of follow-up visits honored over a two-year period from the time of healing

- Recurrence of foot wounds Hospitalization for foot wounds

- Pedicure follow-up

- Appropriate footwear.

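### The 2-year recurrence comparison rests on unadjusted tests between groups formed by attendance; the only adjusted model is conditional and not named as primary

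*Protocol*

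**What the plan says.** The Objectives section of the protocol sets a causal aim: "To evaluate the benefit of a specific multidisciplinary follow-up of the healed diabetic foot", at two consultations a year, on wound recurrence. The primary outcome is binary: "Foot wound recurrence at 2 years". The design is stated as "Monocentric retrospective cohort study, observational study".

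Nobody is allocated to a group. Under Description of the statistical methods, the experimental group is "Patients who have attended at least an average of 2 consultations per year for 2 years, i.e. a minimum of 4 sessions over 2 years". For everyone else: "Patients who do not reach this number will be included in the control group". Nature of data collected shows when attendance is counted: "Number of follow-up visits honored over a two-year period from the time of healing".

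The same methods section then plans three layers of analysis:

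- For the 2-year rates of recurrence and of the three secondary outcomes: "The rates of recurrence, hospitalization, pedicure follow-up and adapted footwear will be compared between the 2 groups by Fisher exact tests".
- For time to recurrence, Kaplan-Meier curves and a log-rank test, with no covariates.
- "If the conditions for application are met, the time to recurrence will be analyzed by a multivariate Cox regression model". Its terms are age, sex, diabetes duration, arterial disease, neuropathy, follow-up group, pedicure and adapted shoes.

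No analysis is designated as primary. The conditions for running the Cox model are not defined, and nothing is said about what happens if they are not met.

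**The concern.** Patients who keep four or more appointments in two years probably differ from those who do not, in disease severity, general adherence and intensity of recall. A crude comparison then mixes any effect of the consultations with those differences. The bias can go either way: more adherent, lower-risk patients may attend more, or higher-risk patients may be recalled more often.

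The protocol recognises this in part, because it lists five patient characteristics for the Cox model. Yet the test it names for its own primary outcome uses none of them, and the adjusted model is conditional. Followed as written, the plan could report a crude p-value as the answer to a question about benefit.

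**Working it through.** **1. Which analyses adjust for anything?** The protocol derives no figure on this point, so there is none to reproduce. The planned analyses compare as follows.

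| Quantity | Planned analysis | Adjusted? | Conditional? |
|---|---|---|---|
| 2-year recurrence (primary outcome) | Fisher | No | No |
| Time to recurrence | Kaplan-Meier, log-rank | No | No |
| Time to recurrence | Cox, 8 terms | Yes | Yes, conditions undefined |
| Hospitalization, pedicure, footwear | Fisher | No | No |

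**2. Could the Cox conditions fail?** Sparse events are one plausible reason. Inputs from the protocol are 158 patients and 8 model terms (5 characteristics, group, pedicure, shoes). The overall 2-year recurrence rate is not given, so a range is assumed. Events per term = 158 × rate / 8.

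- 25%: 158 × 0.25 / 8 = 4.9
- 40%: 158 × 0.40 / 8 = 7.9
- 46%, from the stated 60% at 3 years under an assumed constant hazard, 1 − 0.40^(2/3) = 0.457: 158 × 0.457 / 8 = 9.0
- 54%, from the stated 1-year rates under the same assumption, 1 − 0.75² = 0.4375 and 1 − 0.60² = 0.64, averaged: 158 × 0.54 / 8 = 10.7

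So a failed check is plausible but not certain.

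**3. How far could confounding move the crude result?** Every input here is assumed except the total of 158. Suppose attendance has no effect, and one binary risk factor is more common in non-attenders. The crude rate in a group is prevalence × high risk + (1 − prevalence) × low risk. The rejection rate is the exact probability that a two-sided 5% Fisher test rejects with 79 v 79 patients (equal split assumed).

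| Low / high risk | Prevalence, attenders v non-attenders | Crude rates | Gap | Fisher rejects |
|---|---|---|---|---|
| 45% in both groups | balanced | 45% v 45% | 0 | 3.2% |
| 30% / 60% | 40% v 60% | 42% v 48% | 6 points | 8.4% |
| 40% / 62% | 35% v 65% | 47.7% v 54.3% | 6.6 points | 9.5% |
| 30% / 60% | 30% v 70% | 39% v 51% | 12 points | 26% |
| 20% / 70% | 30% v 70% | 35% v 55% | 20 points | 65% |

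The third row in full: 0.35 × 0.62 + 0.65 × 0.40 = 0.477, and 0.65 × 0.62 + 0.35 × 0.40 = 0.543. Swapping the prevalences gives a spurious harm of the same size. With a 2:1 split (105 v 53), that row rejects in about 11% of studies, against 4% when both rates are 51%.

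**4. Does the Cox model, when run, answer the primary objective?** Only in part.

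- It concerns time to recurrence, not the 2-year risk.
- It adjusts for pedicure and adapted shoes. The secondary objectives name these as things the follow-up is meant to improve, so the group coefficient would not be the total benefit.
- It omits history of amputation, HbA1c and diabetes type, although all three are collected.
- Attendance is counted over the same two years as recurrence. A patient's group therefore depends on what happens after time zero, and baseline covariates do not repair that.

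**The case against.** The strongest reply is that the protocol does plan to adjust. Its Cox model includes the follow-up group and five relevant characteristics, and the descriptive comparisons would reveal imbalance in the collected factors. What to do when a model assumption fails, and whether secondary outcomes get adjusted models, are often settled in a statistical analysis plan. One may exist here but is not shown. This stands: the missing fallback and the missing adjusted secondary analyses are not counted as defects here.

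Three stronger readings are tempting, and the protocol does not support them.

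- **That Fisher is the only test bearing on recurrence.** It is the only one of the binary 2-year rate, but a log-rank test and a Cox model also address recurrence.
- **That adjustment is dropped if the Cox conditions fail.** The text makes the model conditional and is silent on the alternative. It does not mention proportional hazards.
- **That the primary result is confounded as a matter of fact.** No imbalance data are given, and the direction of any bias is unknown.

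It would also be wrong to set the 6.6 points against the 15-point difference implied by 25% v 40% in the justification section. Those are 1-year rates, while the illustration concerns the 2-year outcome. In that example a false-positive result is also still unlikely, at about 9%.

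What the reply does not remove is that the protocol itself names a crude test for the primary outcome and gives the adjusted model no primary standing.

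**Conclusion.** The point holds in a limited form. The 2-year recurrence comparison rests on an unadjusted Fisher test, supported by an unadjusted log-rank test, between groups formed by patients' own attendance. The only adjusted analysis addresses time to recurrence, depends on undefined conditions and is not designated primary. The conclusion about benefit is therefore open to confounding, in either direction.

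The size is not known. The illustrations run from a 6-point to a 20-point spurious gap and from 8% to 65% false rejection. They rest on assumed risks, prevalences and group split, and show what is possible rather than what is expected. That the Cox model may not be run is likewise plausible only, at 4.9 to 10.7 events per term over assumed recurrence rates.

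**What to change.** In Description of the statistical methods:

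- Designate as primary an adjusted comparison of 2-year recurrence, for example a standardised or inverse-probability-weighted risk difference with 95% CI. Another adjusted method would serve if it targets the 2-year risk.
- Adjust for baseline factors already collected: age, sex, diabetes type and duration, arterial disease, neuropathy, history of amputation, and HbA1c where measured at baseline. Leave out pedicure and footwear, because they are outcomes of the follow-up.
- Do not make adjustment depend on the Cox conditions. Keep the Fisher and log-rank tests as descriptive.
- State that baseline adjustment does not remove the bias from counting visits over the same two years as recurrence. That needs its own correction, for example a landmark analysis or a time-dependent exposure.
- State that residual confounding remains. The data list contains no severity measure for the index wound and no separate measure of adherence.

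The cost is revised wording, slightly more analysis work and possibly a wider interval than the crude comparison gives. The covariates are already on the collection list; the landmark or time-dependent correction would also need visit dates, which that list does not name.

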###### Study population

- - 1. **Inclusion criteria**
- Patient with a type 1 or 2 follow-up at the Centre Hospitalier Sud-FranciIien (CHSF),
- Discharge from hospital from a foot wound between 2017 and 2019 with a 2 years post-healing follow-up
- Age greater than or equal to 18 years,
- People not deprived of liberty,
- Subject informed of the study and did not object.

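### The Cox model omits, without a reason, collected baseline variables, chiefly history of amputation, leaving possible residual confounding in the only adjusted comparison

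*Protocol*

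**What the plan says.** The protocol's section on the nature of data collected lists eight baseline characteristics: age, gender, type of diabetes, duration of diabetes, arterial disease, neuropathy, amputation history and HbA1c. The relevant entries read "History of amputation" and "Type and duration of diabetes"; HbA1c has its own line. All stand above a separate heading for items recorded during the 2-year observation period.

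The description of the statistical methods says: "If the conditions for application are met, the time to recurrence will be analyzed by a multivariate Cox regression model". The model takes into account "the characteristics of the patients (age, sex, length of diabetes, presence of arterial disease, neuropathy", then remission-clinic follow-up (the exposure), then "whether they had pedicures and whether they wore adapted shoes". The list is given twice with the same content. Neither version contains amputation history, HbA1c or diabetes type, and no reason or selection rule is stated.

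On grouping, the same section says: "The 2 groups will be defined according to the number of consultations honored each year over a 2-year period". Recurrence and the other rates "will be compared between the 2 groups by Fisher exact tests", and time to recurrence is also compared by a log-rank test. Neither comparison is adjusted.

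**The concern.** Whether a patient keeps at least four visits in two years may depend on how severe the foot disease has been and on how well the patient adheres to care. Both may also bear on recurrence. The primary objective is to evaluate a benefit of follow-up, so any causal reading rests on the adjusted estimate, and that estimate depends on its covariate set.

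Amputation history is the clearest omission: it records past foot-disease severity and could plausibly lead both to closer follow-up and to more recurrence. HbA1c could plausibly reflect adherence. Diabetes type matters less. It varies in the cohort, since the inclusion criterion reads "Patient with a type 1 or 2 follow-up at the Centre Hospitalier Sud-FranciIien (CHSF", but age and duration, both in the model, may capture part of it.

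The list is also oddly balanced. It leaves out variables that precede the exposure but includes pedicure care and footwear, which are recorded during follow-up and are themselves secondary outcomes.

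**Working it through.** **1. Collected versus modelled.** Eight baseline characteristics are collected and five are in the model, so three are left out. The model has 5 patient characteristics + 1 exposure + 2 care variables = 8 terms.

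**2. Illustrative size of the bias.** The protocol gives no prevalence or prognostic effect for the omitted variables, so the values below are assumptions. For one omitted binary factor with recurrence hazard ratio g and prevalence p1 (experimental) and p0 (control), the group hazard ratio is multiplied by approximately

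(1 + p1(g − 1)) / (1 + p0(g − 1)).

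For g = 2 and 40% versus 20%: 1.4/1.2 = 1.17. Reversed: 1.2/1.4 = 0.86.

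| g | 30% vs 30% | 20% vs 30% | 20% vs 40% | 40% vs 20% |
|---|---|---|---|---|
| 1.5 | 1.00 | 0.96 | 0.92 | 1.09 |
| 2 | 1.00 | 0.92 | 0.86 | 1.17 |
| 2.5 | 1.00 | 0.90 | 0.81 | 1.23 |

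The formula is approximate and treats the whole imbalance as unadjusted. Only the imbalance that remains after conditioning on age, sex, diabetes duration, arterial disease and neuropathy would count, so these factors tend to overstate the effect.

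**3. Can the model carry more terms?** The planned number is 158 patients (protocol summary), with no size calculation. The protocol's recurrence figures are 25% and 40% at 1 year (section on expected outcomes) and 60% at 3 years (summary). Assuming a constant hazard, the 2-year events are:

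- 25% per year: 1 − 0.75² = 0.4375; × 158 = 69.1
- 60% at 3 years: 1 − 0.40^(2/3) = 0.457; × 158 = 72.2
- 40% per year: 1 − 0.60² = 0.64; × 158 = 101.1

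The first and last put the whole cohort at one group's rate, so they bracket any mix of the two.

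| Model | Terms | 69.1 events | 72.2 events | 101.1 events |
|---|---|---|---|---|
| As written | 8 | 8.6 | 9.0 | 12.6 |
| All three added, pedicure and footwear removed | 9 | 7.7 | 8.0 | 11.2 |
| Amputation and HbA1c added, nothing removed | 10 | 6.9 | 7.2 | 10.1 |
| All three added, nothing removed | 11 | 6.3 | 6.6 | 9.2 |

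Entries are events per term. Adding amputation and HbA1c while removing pedicure and footwear leaves 8 terms, as now.

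**The case against.** The strongest reply is that nothing in the protocol links the three variables to attendance or to recurrence. That is correct. A reader might infer that the omission leaves established confounding in the estimate, or that it biases the result in a particular direction. The documents support neither: no imbalance or prognostic effect is shown, and the bias may be nil.

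Other points stand in part:

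- Arterial disease, neuropathy, age and duration may already absorb some of what the omitted variables carry, most obviously for diabetes type.
- HbA1c has no stated measurement date and comes from routine records, so missing values could cost patients in a complete-case fit.
- With roughly 69 to 101 events, a short covariate list is defensible, but the protocol does not give that reason.
- The planned descriptive comparisons could show an imbalance in these variables, but would not adjust for it.
- The Cox model runs only if its conditions are met, and the change would not touch the Fisher or log-rank results.

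It can also be said that covariates belong in the statistical analysis plan. That would answer a protocol that was silent. This one names a specific set, and the point concerns what it names.

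**Conclusion.** The point holds as a weakness in the adjusted analysis. Three collected baseline variables are left out of the named Cox list without a reason, in a non-randomised comparison whose only adjusted estimate comes from that model. The consequence is possible residual confounding of unknown size and sign. Under the assumed values tabulated, the group hazard ratio would be multiplied by 0.81 to 1.23, and by 1.00 with no imbalance. These factors are illustrations, not estimates.

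The case is strongest for amputation history, weaker for HbA1c and weakest for diabetes type. A reader might also infer that fuller adjustment would make the comparison sound. It would not, because groups would still be defined by visits counted during follow-up.

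**What to change.** Add history of amputation (as at healing) and HbA1c (last value at or before healing) to the prespecified baseline covariates of the main Cox model. State how missing HbA1c will be handled so that patients are not dropped, for example by multiple imputation. Make diabetes type optional or put it in a sensitivity analysis. Give a one-line reason for each collected baseline variable that is still left out.

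Take pedicure care and footwear out of the main adjusted model. They are recorded during follow-up and are secondary outcomes, and removing them frees two terms.

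No new data are needed. The cost is in model size and missing-data handling. Without the removal, all three additions give 11 terms and about 6.3 to 9.2 events per term. With it, the model has 9 terms and about 7.7 to 11.2, against 8.6 to 12.6 now. If events prove fewer, amputation history alone costs one term and is the addition to keep; a propensity score or penalised model is an alternative.

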#### Secondary objectives

Evaluate the benefit of a specific multidisciplinary follow-up of the healed diabetic foot at the rate of 2 annual consultations on :

- recurrence with the need for hospitalization.
- pedicure follow-uo of patients.
- wearing suitable footwear.

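### The Cox model adjusts the follow-up effect for pedicure care and adapted shoes, which the protocol lists as outcomes of that follow-up, so its coefficient leaves out any benefit that passes through them

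*Protocol*

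**What the plan says.** The primary objective (Protocol, *Objectives*) is "To evaluate the benefit of a specific multidisciplinary follow-up of the healed diabetic foot at the rate of 2 annual consultations on wound recurrence". The *Secondary objectives* ask for the benefit of the same follow-up on, among other things, "pedicure follow-uo of patients" and "wearing suitable footwear". The *Secondary outcomes* accordingly list "Pedicure follow-up at 2 years" and "Wearing suitable footwear at 2 years".

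Under *Nature of data collected*, age, gender, diabetes type and duration, arterial disease, neuropathy, amputation history and HbA1c come first. Pedicure follow-up and footwear come in a second block, covering the 2 years from healing, together with visits honoured, recurrence and hospitalisation. No pedicure or footwear status at healing is listed.

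*Description of the statistical methods* uses these two variables in two ways. They are compared between groups by Fisher's exact test, as outcomes. They are also entered in a multivariable Cox model of time to recurrence, to be run if its conditions are met. That model contains "the characteristics of the patients (age, sex, length of diabetes, presence of arterial disease, neuropathy"), the follow-up term, and "whether they had pedicures and whether they wore adapted shoes". The covariate list appears in two consecutive paragraphs with the same content.

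**The concern.** A variable that the exposure is expected to change, and that may itself change the outcome, lies on the causal path. Holding it fixed leaves a coefficient for the effect of follow-up that does not pass through it. The primary objective asks a different question: what the follow-up does to recurrence as a whole, including anything it achieves by getting patients into pedicure care and suitable shoes.

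Timing is a second difficulty. Both variables are established at some point in the 2 years after healing. Entered as fixed yes/no covariates from healing, they let the model use information that did not yet exist at time zero.

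This matters because groups are formed by attendance rather than by randomisation. The unadjusted comparisons cannot separate the follow-up from the kind of patient who attends. The Cox model is the one analysis in the protocol that tries to, so readers are likely to rely on its follow-up coefficient.

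**Working it through.** The protocol gives no target hazard ratio, power or sample size calculation, so there is no figure of its own to reproduce. The check has three parts.

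**1. Role of each variable, side by side**

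| Variable | Objectives and outcomes | When recorded | Role in the Cox model |
|---|---|---|---|
| Follow-up | Exposure in all objectives | 2 years after healing | Exposure term |
| Age, sex, diabetes duration, arterial disease, neuropathy | None | Outside the 2-year block | Covariates |
| Pedicure care | Secondary outcome of follow-up | 2 years after healing | Covariate |
| Adapted footwear | Secondary outcome of follow-up | 2 years after healing | Covariate |

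The last two rows conflict: the same variable is an effect of the exposure and an adjustment for it. No Cox model without them, and no time-dependent handling, is described.

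**2. What the model would target**

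Inputs: 25% recurrence at 1 year with the follow-up and 40% with conventional follow-up (Protocol, section 1 on expected outcomes and hypotheses). Assumptions: constant hazards, and a share m of the log hazard ratio passing through pedicure care and footwear.

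- Total HR = ln(1 − 0.25) / ln(1 − 0.40) = (−0.2877) / (−0.5108) = 0.563.
- HR left after adjustment = 0.563^(1 − m).

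| m (assumed) | HR targeted |
|---|---|
| 0 | 0.56 |
| 0.5 | 0.563^0.5 = 0.75 |
| 0.75 | 0.563^0.25 = 0.87 |
| 1 | 1.0 |

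**3. Simulation of the mechanism**

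Each scenario used a cohort of 40,000 with exponential times, 2 years of follow-up and two binary mediators drawn independently within group. Every effect size and uptake rate is assumed, since the documents give none. Uptake is control versus follow-up, the same for both mediators. The Cox model was fitted without and with the two mediators.

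| Direct HR | HR per mediator | Uptake | Follow-up HR without | Follow-up HR with | Log-HR removed |
|---|---|---|---|---|---|
| 1.0 | 0.5 | 40% vs 80% | 0.57 | 0.99 | 98% |
| 0.8 | 0.5 | 40% vs 80% | 0.45 | 0.80 | 71% |
| 0.8 | 0.7 | 50% vs 60% | 0.74 | 0.79 | 22% |
| 0.6 | 0.5 | 40% vs 80% | 0.35 | 0.58 | 48% |
| 0.6 | 0.7 | 50% vs 60% | 0.58 | 0.61 | 11% |
| 0.8 | 1.0 | 40% vs 80% | 0.80 | 0.80 | 1% |
| 0.8 | 0.7 | 50% vs 50% | 0.79 | 0.79 | −1% |

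The model with mediators returns the direct effect, within simulation error. With a direct effect present, differing uptake and active mediators, 11% to 71% of the log hazard ratio is lost. With no direct effect, essentially all of it is lost. With equal uptake, or mediators that do not affect recurrence, nothing material is lost.

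**The case against.** Several points can fairly be made in the plan's defence.

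- **The comparison of the primary outcome is untouched.** Recurrence is compared by Fisher's exact test and time to recurrence by Kaplan-Meier and log-rank, none of which uses pedicure care or footwear. The Cox model is conditional. This stands, and it confines the point to the adjusted estimate. It does not remove the point, because those comparisons do not control confounding.
- **The two variables may not be pure mediators.** Visits accrue over the same 2 years, so pedicure care or shoes may come before, during or after them. They may also mark general adherence, which could confound a group defined by attendance. This stands as a caution: dropping them may leave some confounding. It does not justify fixed covariates measured after healing. Status at healing would be the proper adjustment, and the present model can be kept as an exploratory one.
- **The covariate list could be read as a descriptive model of factors associated with recurrence, and a separate analysis plan might specify a baseline-only model.** Either is possible. But the protocol states the covariates explicitly and names no other adjusted model, so the statement is restricted to what the protocol describes.

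A reader might infer more: that the adjusted model removes the whole benefit, or that an effective programme would be reported as having no effect. The documents do not support this. It requires full or nearly full mediation, and nothing in the protocol says that follow-up works mainly through pedicure care and shoes; its hypothesis credits the consultations as a whole. A reader might also suppose that shoes or pedicure care were prescribed because of a recurrence. That would worsen the timing problem, but the protocol does not say it happens.

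**Conclusion.** The covariate list is wrong as written for the stated objective. The protocol treats pedicure care and footwear as outcomes of the follow-up and also adjusts for them, so the follow-up coefficient excludes the part of any benefit that runs through them and conditions on information from after time zero. As a result, the protocol describes no confounder-adjusted estimate of the total effect.

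The size cannot be fixed from the documents. From a total hazard ratio of about 0.56, the targeted value ranges from 0.56 with no mediation, through 0.75 at a half share and 0.87 at three quarters, to 1.0 at full mediation. This rests on constant hazards, on the protocol's 1-year rates and on an assumed mediated share. The loss is small if uptake does not differ between groups or if neither variable affects recurrence, although the secondary objectives anticipate an effect on uptake. No power figure is offered: the documents give neither a group split nor expected 2-year recurrence by group, and the issue is which effect is estimated.

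**What to change.** In *Description of the statistical methods*, in both paragraphs that carry the covariate list:

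- Define the main Cox model as the follow-up term plus characteristics known at healing only: age, sex, length of diabetes, arterial disease and neuropathy. Add pedicure and footwear status at healing if the records hold it.
- Keep the 2-year pedicure and footwear values as secondary outcomes.
- Show any model containing those 2-year values only as a labelled exploratory direct-effect analysis, with both variables handled as time-dependent where dates exist.

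The cost is a rewording of the covariate list and, optionally, two yes/no baseline items from the same records. Nothing is lost, since the present model can still be reported under its proper label.

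Two limits should be stated with the change. Some adherence-related confounding may remain. The change also does not cure a separate problem: the follow-up group is itself defined by at least 4 visits honoured over the same 2 years in which recurrence is counted. That needs its own remedy before the follow-up coefficient can be read as a total effect.
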